### Randomization

Using stratified block randomization (block size of 6) [21], participants are assigned into 1 of the 2 equal-size age-, sex-, and severity-matched groups: group 1 and group 2 (Table 1). Balanced randomization is applied within each block, such that 3 participants receive the active transcranial alternating current stimulation treatment and the rest receive the sham treatment. This randomization procedure is used to avoid bias in statistical analyses comparing the 2 groups.

**Table 1 table1:** Stratified blocks using 2 levels for 3 factors.

Block number	Factor		
	Age (years)	Sex	Severity (Montreal Cognitive Assessment score)
1	≥70	Female	≥18
2	≥70	Female	<18
3	≥70	Male	≥18
4	≥70	Male	<18
5	<70	Female	≥18
6	<70	Female	<18
7	<70	Male	≥18
8	<70	Male	<18

### Treatment Protocol

Training for all groups occurs in-person over the course of 4 weeks, 5 days per week (excluding weekends); there is an 8-week wash-out period prior to group crossover. On each day, participants attend two 30-minute training sessions using an app (MindTriggers) with a 30-minute break in between. Assessments occur at baseline (week 0), postintervention (weeks 5 and 11), at a follow-up (week 16), and at a long-term follow-up (week 27). Assessment at week 11 is considered to be baseline for the second cycle. No crossover occurs for participants assigned to group 3 (Figure 1).

**Figure 1 figure1:**
[figure not shown]
Study flowchart for groups 1 to 3.

During a learning or problem-solving task, it has been shown that gamma band waves (brain waves faster than 30 Hz) are generated [22]. Previous work has suggested the potential of gamma band stimulation to improve cognitive performance in dementia patients [23], improve working memory [24], and increase attentiveness [25]. Furthermore, the reduction of intracerebral tau protein burden has been proposed as an added benefit of gamma band stimulation [26]. Transcranial alternating current stimulation is one such means of gamma band stimulation. Recent work [14] further supported cognitive improvement in older adults with more sustained improvement in participants who underwent transcranial alternating current stimulation. However, the use of small sample sizes in all studies [14,23-26] limited the conclusions that could be drawn. Thus, given the benefits of gamma band stimulation, transcranial alternating current stimulation is applied at a frequency of 40 Hz with a current density of 0.04 mA/cm^2^.

Therefore, participants in group 1 and group 2 receive transcranial alternating current stimulation treatment simultaneously with cognitive exercises. The transcranial alternating current stimulation treatment (Model 2001; Soterix Medication) is applied with a sinusoidal waveform at 40 Hz, with a current amplitude of –0.75 mA to 0.75 mA (1.5 mA peak-to-peak). Electrode placement is measured at the first training session, with the active electrode being placed over the left dorsolateral prefrontal cortex, and the reference electrode being placed on the contralateral supraorbital area.

To prevent unblinding, the auto-sham toggle on the transcranial alternating current stimulation machine is hidden from assessors with a physical barrier. The auto-sham sequence provides the same sensory experience as active transcranial alternating current stimulation by providing a ramp up and down to 1.5 mA at the start of treatment, and again after 10 minutes.

### Outcome Measures

At each assessment, 9 tests are conducted over 2 days due to time constraints. The first assessment day comprises the Wechsler Memory Scale Older Adult Battery [27], Montgomery-Åsberg Depression Rating Scale, a verbal fluency test for speech analysis, a visual 1-back task [28], virtual reality navigation [29], the Neuropsychiatric Inventory Questionnaire, and functional near-infrared spectroscopy. The second assessment day includes electrovestibulography and the Alzheimer Disease Assessment Scale (ADAS) cognitive subscale. An assessor is assigned to each participant and performs all 4 assessments with the assigned participant. Only the study participant and the research personnel designated to administer assessments are present during assessments.

The primary outcomes are the changes in patients’ scores from baseline in the Wechsler Memory Scale Older Adult Battery and ADAS cognitive subscale assessments. Alternate forms of the ADAS cognitive subscale word lists are employed at each visit to reduce possible practice effects. The secondary outcomes are change in 1-back, Neuropsychiatric Inventory Questionnaire, and Montgomery-Åsberg Depression Rating Scale performance. The 1-back test presents a sequence of random shapes and participants must recall whether a presented object is a repeat of the previous object [28]. Neuropsychiatric Inventory Questionnaire is used to assesses neuropsychiatric symptoms and caregiver burden. Finally, to establish the presence of confounding variables, namely mood disorders, Montgomery-Åsberg Depression Rating Scale is evaluated at each assessment. The secondary exploratory outcome measures use a series of physiological monitoring tools to examine physiological changes in study participants before and after the intervention: (1) virtual reality navigation test to assess spatial orientation [29], (2) electrovestibulography [30-32] to assess static and dynamic vestibular response, (3) functional near-infrared spectroscopy (OctaMonas) [33] to record prefrontal cortex brain activities, and (4) verbal fluency to evaluate acoustic and linguistic changes (Table 2). It should be noted that the exploratory assessments will only be conducted at the Manitoba site.

**Table 2 table2:** Study outcome measures.

Outcome measures		Assessments
**Primary**		
	Wechsler Memory Scale Older Adult Battery	Older adult memory
	Alzheimer Disease Assessment Scale cognitive subscale	Cognitive dysfunction level in Alzheimer disease
**Secondary**		
	Visual 1-back task	Immediate recall
	Neuropsychiatric Inventory Questionnaire	Neuropsychiatric symptoms; caregiver burden
	Montgomery-Åsberg Depression Rating Scale	Mood disorders
**Exploratory**		
	Functional near-infrared spectroscopy	Functional brain activity
	Virtual reality navigation	Spatial orientation
	Electrovestibulography	Static and dynamic vestibular response
	Verbal fluency	Acoustic and linguistic changes

#### Virtual Reality Navigation as a Test for Spatial Orientation

Virtual reality navigation assists in the detection of cognitive impairment by measuring how people orient themselves in an unfamiliar environment [29]. The virtual reality navigation test has two stages of assessment, which are completed on a laptop: (1) target localization from outside a building, and (2) target location inside a building.

#### Electrovestibulography

Electrovestibulography is a noninvasive recording made from the vestibulo-acoustic system with no motion and with passive whole-body tilt [30-32]. For this study, measurements are performed before and after treatment in order to assess the ability of electrovestibulography to predict treatment outcomes.

#### Functional Near-Infrared Spectroscopy

Functional near-infrared spectroscopy is an optical technique that uses near-infrared light, which is capable of penetrating the scalp, skull, and other brain tissues to reach gray matter, in order to noninvasively monitor functional brain activity by measuring the flow of oxygenated and deoxygenated blood [33]. Its main benefits are portability, noninvasiveness, and relatively high temporal resolution (100 ms) [33].

### Safety Considerations

The transcranial alternating current stimulation procedure used in this study is of minimal risk, though discomfort may arise. Common adverse effects of transcranial alternating current stimulation include mild headache, facial twitches, itching, redness under the electrodes, and light flashes [18]. The application of transcranial alternating current stimulation should be stopped if facial twitches or light flashes are experienced by the participant. Participants are asked at each visit if they have experienced any adverse effects from the treatment. Participants’ self-assessment of any pain or discomfort from the treatment are also recorded at every visit. To match similar studies [34], participant transcranial alternating current stimulation sensations are rated on a scale from 1 to 5 at each session, with 1 indicating no sensations, 2 indicating mild sensations, 3 indicating moderate sensations, 4 indicating strong sensations, and 5 indicating very strong sensations.

Assessment technologies also incur minimal risk. Dizziness may occur during virtual reality navigation, the head band used in functional near-infrared spectroscopy may cause discomfort, and electrovestibulography can result in ear infection if the ears are not properly cleaned after the assessment. In the case of any unexpected issue, or pain and intolerance experienced by a participant, assessments will be halted and risks will be reassessed. All issues will be reported to the appropriate ethics board.

### Statistical Analysis

#### Sample Size Estimation

This study will have 2 equal-sized groups, and it is hypothesized that one group’s mean will be significantly different from the other's in one primary outcome measure. As such, the sample size for each group can be calculated [35]. The expected difference and standard deviation for Wechsler Memory Scale Older Adult Battery mean scores between the 2 groups were 20 and 38, respectively, based on the results from a pilot study [14], from which individuals with a Montreal Cognitive Assessment score <5 were removed. With a test power of 80% and significance of 5%, the minimum sample size was estimated as 58 per group. However, due to the study’s crossover design, this number was halved. Allowing for a 5% dropout rate, and 20% transcranial alternating current stimulation intolerance rate [14], a total of 75 participants should be enrolled across all 3 groups. Of the total participants, approximately 30 are expected to be recruited at the Alberta study site, and the remaining participants are expected to be recruited at the Manitoba study site.

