**Methods:**

We will recruit and enroll 75 participants (older than 50 years old with either mild cognitive impairment or probable early or moderate dementia) for this double-blind randomized controlled study to estimate the efficacy of active transcranial alternating current stimulation with cognitive treatment (in comparison with sham transcranial alternating current stimulation). This will be a crossover study; a cycle consists of sham or active treatment for a period of 4 weeks (5 days per week, in two 30-minute sessions with a half-hour break in between), and participants are randomized into 2 groups, with stratification by age, sex, and cognitive level (measured with the Montreal Cognitive Assessment). Outcomes will be assessed before and after each treatment cycle. The primary outcomes are changes in Wechsler Memory Scale Older Adult Battery and Alzheimer Disease Assessment Scale scores. Secondary outcomes are changes in performance on tests of frontal lobe functioning (verbal fluency), neuropsychiatric symptoms (Neuropsychiatric Inventory Questionnaire), mood changes (Montgomery-Åsberg Depression Rating Scale), and short-term recall (visual 1-back task). Exploratory outcome measures will also be assessed: static and dynamic vestibular response using electrovestibulography, neuronal changes using functional near-infrared spectroscopy, and change in spatial orientation using virtual reality navigation.

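### Two primary outcomes are named, but the sizing hypothesis asks for a difference in only one at an unsplit 5%, and nothing says which outcome decides or whether both must be significant

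*Protocol article*

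**What the plan says.** The abstract lists two primary outcomes: "The primary outcomes are changes in Wechsler Memory Scale Older Adult Battery and Alzheimer Disease Assessment Scale scores". The Outcome Measures section repeats the pair as changes in "scores from baseline in the Wechsler Memory Scale Older Adult Battery and ADAS cognitive subscale assessments", and Table 2 puts both under the primary heading. Neither is ranked above the other.

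The Sample Size Estimation section hypothesises that the group means will differ significantly "in one primary outcome measure". That sentence does not name the measure. The planning figures that follow are for the Wechsler scale only: the difference and SD of "mean scores between the 2 groups were 20 and 38, respectively". The section continues: "With a test power of 80% and significance of 5%, the minimum sample size was estimated as 58 per group". It then says that "due to the study’s crossover design, this number was halved". ADAS has no planning difference or SD.

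This 5% is the only significance level in the document. The Analysis section describes models and tests but gives no level and does not say how the two primary results combine. The Hypotheses section speaks of cognitive performance and cognitive improvement without naming a scale.

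**The concern.** With two primary outcomes, the plan has to settle one of three things: one outcome decides, both must be significant, or either suffices with the error rate controlled across the two. The only sentence that bears on this asks for a difference in one of them, next to an undivided 5%. Taken at its word, significance on either scale meets the stated hypothesis. The 5% used for sizing is then not the error rate of the trial's conclusion, and a result on one scale alone could be reported as confirmatory.

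The choice also affects the sample size. Dividing the 5% between the scales lowers the power of the Wechsler comparison that the planned number was built on, whereas a fixed order starting with Wechsler does not.

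**Working it through.** **Inputs from the protocol.** Wechsler difference 20, SD 38, power 80%, significance 5%, 58 per group before halving (all Sample Size Estimation). There are two primary outcomes (abstract, Outcome Measures, Table 2).

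**Assumptions, not in the protocol.** The correlation r between the two test statistics under the null, shown from 0 to 0.9. The correlation ρ between a participant's results in the two cycles, shown at 0 and 0.5, with SD 38 applying to each cycle.

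**1. The protocol's own figure.** n per group = 2 × [38 × (1.960 + 0.842) / 20]² = 56.7, so 57 by the normal approximation. The t-based calculation gives 58 (power 80.2%), as stated. A one-sided 5% test would give 45, so the 5% is two-sided. Halving 58 per group gives 29 per group, 58 participants in all.

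**2. Familywise error if either scale suffices at two-sided 5%.** At r = 0 it is 1 − 0.95² = 0.0975. For r > 0 it is the bivariate normal probability that |Z₁| or |Z₂| exceeds 1.96. For errors favouring active, both statistics are oriented so that positive means benefit, and the probability is that Z₁ or Z₂ exceeds 1.96.

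| Assumed r | Either direction (nominal 5%) | Favouring active (nominal 2.5%) |
|---|---|---|
| 0 | 9.75% | 4.9% |
| 0.3 | 9.5% | 4.8% |
| 0.5 | 9.1% | 4.5% |
| 0.7 | 8.3% | 4.2% |
| 0.8 | 7.8% | 3.9% |
| 0.9 | 7.0% | 3.5% |

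The rate falls to the nominal level only at r = 1.

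**3. Splitting the 5% into 2.5% per scale.** At r = 0 the familywise error is 1 − 0.975² = 4.94%, so a split controls it. For power on Wechsler with 58 participants each contributing both cycles, the standard error of the active-sham difference is 38 × √[2(1 − ρ)/58].

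- ρ = 0: standard error 7.06, noncentrality 20/7.06 = 2.83. On 56 degrees of freedom, power is 79.5% at 5% and 70.2% at 2.5%.
- ρ = 0.5: standard error 4.99, noncentrality 20/4.99 = 4.01. Power is 97.6% at 5% and 95.3% at 2.5%.

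**4. Fixed order, Wechsler first.** If there is no true Wechsler difference, no false claim on either scale can arise without a false Wechsler result, which has probability 5%. If there is a true Wechsler difference, the only possible false claim is on ADAS, tested at 5%. The familywise error is therefore at most 5%, and Wechsler power is what it would be with Wechsler as the only test.

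**The case against.** The strongest objection is that the quoted phrase may only describe sizing. It stands in the sample size section, the next sentence turns to calculating the group size, and the figures that follow are all Wechsler. On that reading it is not a success criterion, and what remains is silence on multiplicity, which a journal article may leave to an analysis plan that is not shown. The reading is possible. It does not settle the matter, because both scales stay primary with equal rank and the only stated hypothesis is one that either scale satisfies. An unseen analysis plan would have to be reconciled with that wording, and if it split the 5%, it would use a level for which this sample size was not calculated.

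A reader might infer that each scale is tested at 5% and that the chance of falsely declaring efficacy is close to 10%. The document does not support that as a statement of fact. It gives no level for the ADAS test. The 9.75% needs independence, which is unlikely for two cognitive scales measured in the same participants. It also counts errors in both directions, and falsely favouring active stimulation is at most 4.9%.

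Two further points stand. The fall in power to about 70% under a split is the case of uncorrelated cycles, and the loss is smaller if cycles are positively correlated. And a fixed order is one valid choice among several: a split, or requiring both scales, would also control the error. Having been sized makes Wechsler the natural first test but does not compel it.

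**Conclusion.** The point holds as a rule that is stated and badly fixed. The protocol has two equal primaries, a hypothesis met by one of them, one undivided 5% level and one sized outcome, and it does not say which outcome decides or whether both must be significant.

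If either scale suffices at two-sided 5%, the familywise error is above 5%: 9.75% at most, about 8% to 9% at assumed correlations of 0.5 to 0.8, and 7.0% at 0.9. For falsely favouring active it is 3.5% to 4.9% against 2.5%. These figures depend on two things that the document does not give: the correlation between the scales, and use of the 5% level for ADAS. The existence of the excess depends on the second but not on the exact correlation, so long as it is below 1.

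**What to change.** In Sample Size Estimation, replace the wording about one primary outcome with a fixed order, and state the same order in Outcome Measures:

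1. Test the active-sham contrast on the Wechsler Memory Scale Older Adult Battery first, at two-sided 5%. It is the only contrast that was sized.
2. Test the ADAS cognitive subscale at two-sided 5% only if the first test is significant. Otherwise report it as an estimate with a confidence interval and make no confirmatory claim.

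The abstract and the trial registration should then agree with this. The cost is a few sentences, with no additional participants or visits and no change in planned Wechsler power. The downside is that a result on ADAS alone could not support a confirmatory claim.

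If the sponsor wants either scale to be able to carry the claim, 2.5% for each also controls the error. The sample size should then be recalculated at 2.5% with a stated between-cycle correlation, because Wechsler power at 58 participants would be about 70% if cycles are uncorrelated and about 95% at an assumed correlation of 0.5.

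With 7 participants enrolled and 4 through baseline assessment on February 10, 2022, almost all outcome data still lay ahead at that date.

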### Analysis

Both parametric and nonparametric statistical techniques will be used. Analysis of the repeated measures crossover data will be performed using fixed and random effect models to investigate different sources of variations in the data set such as period effect, direct treatment effect, and carryover treatment effects [36]. If raw data are found to not be normally distributed, the Box-Cox transformation will be employed to satisfy the normality assumption needed to perform the analysis [37].

In addition, the differences between study cycle data of the basic crossover design will be analyzed (that is, the differences between active and sham transcranial alternating current stimulation results). Study cycle data differences are used to transform the repeated measurements crossover design to a completely randomized repeated measurements design. With the transformed repeated measurements completely randomized design, analysis is completed by a univariate split-plot analysis of variance or multivariate (over time) *F* tests [38]. Should normality be in question due to the relatively small sample size, an alternative approach will be used based on nonparametric tests using ranks [39]. Nonparametric tests will include Wilcoxon rank sum and permutation tests to investigate hypotheses 1 and 2 and examine the absence of carryover effects in the study [39].

To have a better understanding of the data set, baseline measurements will be used to perform analysis of covariance. As such, the baseline crossover differences of each outcome measure (Table 2) are regarded as independent explanatory variables and regression of the basic estimators is calculated on said variables [36].

The abovementioned statistical analysis will be applied to the secondary outcome measures, as well.

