The application of transcranial alternating current stimulation—an external oscillating electrical field that induces cortical activity—either in addition to or independent of brain exercises, on cognition has been explored. It is a relatively inexpensive, easy to administer, and safe tool for noninvasive brain stimulation. Transcranial alternating current stimulation has been demonstrated to both modulate and entrain the ongoing network oscillations in a frequency-specific manner [15], by using appropriate stimulation parameters (ie, frequency, intensity, duration, and anatomical location) to manipulate the phase, the rhythm, and the power of neural oscillations, through in vitro and in vivo experiments [16]. Because it operates in a frequency- and phase-specific manner, which offers the possibility to demonstrate causal relations between oscillations and behavior [17,18], interest in transcranial alternating current stimulation has significantly increased in the past decade. Furthermore, the therapeutic potential of transcranial alternating current stimulation has led many researchers to study its applicability as a treatment option for numerous neurological and psychological disorders [14,18,19]. However, there has been little investigation into the potential effect of transcranial alternating current stimulation on older adults with cognitive impairments associated with dementia. Moreover, much of the research on transcranial alternating current stimulation involves testing participants’ cognitive performance during or immediately after stimulation sessions.

In a recent pilot study [14], we demonstrated that the addition of transcranial alternating current stimulation to a cognitive training program improved participants’ working memory, and improvements remained for a longer period after the intervention; however, there were several shortcomings in this study. Aside from having a limited sample size, the main shortcoming was that placebo effect was not analyzed. We aim to address shortcomings by employing a better study design to investigate the efficacy of combined transcranial alternating current stimulation and cognitive training on the dementia population (Clinicaltrials.gov NCT05203523).

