## Methods

### Experimental Design

This is a randomized, crossover, double-blind, placebo-controlled study. Participants with cognitive impairments are recruited at 1 of 2 sites (Manitoba and Alberta) and randomized into 2 groups, with stratification by age, sex, and cognitive level (measured with Montreal Cognitive Assessment [20]) for randomization. Group 1 participants receive active transcranial alternating current stimulation simultaneously with cognitive exercises. Group 2 participants receive sham transcranial alternating current stimulation simultaneously with cognitive exercises. Participants who cannot tolerate the application of transcranial alternating current stimulation and focus on the cognitive exercises at the same time are enrolled in a third group, in which they only receive cognitive exercises but otherwise follow the same protocol as those in group 1 and group 2. The outcomes of group 3 will be analyzed separately. Standard cognitive assessments are performed before and after treatment, as well as at a scheduled follow-up visit 3 months postintervention. Both participants and assessors remain blind to the type of treatment (active versus placebo) until the end of the study.

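### The sample size is halved on the strength of both cycles, but the first-listed crossover model includes carryover; if the confirmatory estimate comes from that model with one change score per cycle, power is about 50%, not 80%

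*Protocol article*

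**What the plan says.** Under Experimental Design: "This is a randomized, crossover, double-blind, placebo-controlled study". Groups 1 and 2 form two sequences over two treatment cycles; group 3 does not cross over.

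Sample Size Estimation gives the expected difference and standard deviation for the Wechsler Memory Scale Older Adult Battery: "mean scores between the 2 groups were 20 and 38, respectively, based on the results from a pilot study". It continues: "With a test power of 80% and significance of 5%, the minimum sample size was estimated as 58 per group". Then: "However, due to the study’s crossover design, this number was halved". That leaves 29 per sequence, inflated for 5% dropout and 20% intolerance to 75 enrolled.

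The Analysis section first lists models with fixed and random effects, intended to "investigate different sources of variations in the data set such as period effect, direct treatment effect, and carryover treatment effects". It then adds an analysis of active-minus-sham cycle differences, rank and permutation tests that will among other things "examine the absence of carryover effects in the study", and an analysis of covariance on baseline differences. None of these is tied to the 80% power.

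The primary outcomes are changes from baseline (Outcome Measures), and week 11 is the baseline for the second cycle (Treatment Protocol).

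**The concern.** Halving a parallel-group size is a claim that each participant supplies information on both treatments. A free carryover parameter in a two-sequence, two-period design takes that information away, so the halving and a carryover-adjusted confirmatory estimate do not fit together. If the treatment effect were read from that model, the trial could have a roughly even chance of missing the effect it was sized for.

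The check for absence of carryover raises a second problem. If it compares participant totals between sequences, it is a between-participant test at half the parallel-group size. A non-significant result would then be weak support for pooling the cycles. Carryover cannot be dismissed in advance: the Background says of the pilot that "improvements remained for a longer period after the intervention".

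**Working it through.** **Inputs.** From Sample Size Estimation: difference 20, SD 38, power 80%, significance 5%, 58 per group halved to 29. Assumptions: the test is two-sided (the article does not say, but this reproduces its figure), and 38 is the SD of the analysed response.

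**1. The plan's own figure.** n per group = 2(1.96 + 0.842)² × 38² / 20² = 56.7, so 57 by the normal formula. The t-based calculation gives 58 (power 80.2%). The stated 58 is reproduced. Inflation: 57/(0.95 × 0.80) = 75.0 and 58/(0.95 × 0.80) = 76.3, consistent with 75.

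**2. Carryover term in the model, one change score per cycle.** Let m be the mean, p the period 2 effect, t the treatment effect and c the carryover from active into cycle 2. The four cell means are:
- active first: cycle 1 = m + t; cycle 2 = m + p + c
- sham first: cycle 1 = m; cycle 2 = m + p + t

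Four parameters fit four means exactly. Solving, t = (active-first, cycle 1) − (sham-first, cycle 1), with zero weight on cycle 2. A random participant effect does not change this: generalised least squares gives the same standard error at correlations 0, 0.5 and 0.8.
- SE = 38 × √(2/29) = 9.98
- Power for 20 points: 50.4% (noncentral t) or 51.8% (normal)
- Difference detectable with 80% power: about 28.5 points

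**3. No carryover term, both cycles.** SE = ½ × √(2 × 38² × (1 − ρ) × 2/29), with ρ the correlation between a participant's two cycle scores.
- ρ = 0: SE 7.06, power 79.5% (t) or 80.9% (normal)
- ρ = 0.5: SE 4.99, power about 98%

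**4. All four visits modelled (weeks 0, 5, 11, 16).** Assuming compound symmetry, a change-score SD of 38 and a between-visit correlation of 0.5 to 0.8, normal-approximation power is:
- one carryover term common to weeks 11 and 16: 83-87%
- separate carryover terms at those weeks: 56-64%

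If 38 is instead the SD of the raw score, the figures are the same at correlation 0.5 and higher above it.

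**5. The carryover check on participant sums.** SE = √(2 × 38² × (1 + ρ) × 2/29), which is 14.1 at ρ = 0 and 18.4 at ρ = 0.7.
- Carryover of 20 points: power 28.6% to 18.8%
- Carryover of 10 points: power about 11% to 8%

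**6. Direction of bias with change scores.** Take a true effect of 20 and no carryover term. In the active-first sequence the cycle 2 change is shifted by (carryover at week 16 − carryover at week 11). The expected estimate is 20 − ½ × that shift.
- 10 points at both weeks: 20 − ½(0) = 20
- 10 at week 11, gone by week 16: 20 − ½(−10) = 25
- none at week 11, 10 at week 16: 20 − ½(10) = 15

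**The case against.** The strongest reply is that the article never says the confirmatory estimate is carryover-adjusted. It lists carryover as a source of variation to investigate, and its next paragraph plans the active-minus-sham cycle differences, which use both cycles and match the halving. This stands. A reader might infer that the plan as a whole takes the treatment effect from cycle 1 alone; the text does not support that.

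The reply can add that week 11 is a separate cycle 2 baseline and the data are described as repeated measures, so one score per cycle is only one reading. This also stands: step 4 shows that the loss depends on how carryover is coded, and 50% is the low end.

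A reader might also infer that carryover would pull the estimate toward zero by half its size. That holds for raw post-treatment scores. The stated endpoint is change from baseline, for which step 6 shows no bias, bias upward or bias downward, depending on how carryover evolves.

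On the check for absence, the article names the tests but not the contrast, so the 19-29% applies only to participant sums. A week 11 comparison would do better: adjusted for week 0, assuming raw SD 38 and correlation 0.7, it has about 79% power for 20 points. The stated 8-week wash-out also counts against large carryover.

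Finally, naming the primary model may be left to an analysis plan that is not shown. That does not dispose of the point, which concerns two stated elements, a halved sample size and a model with carryover, that fit together only under some readings.

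**Conclusion.** The concern holds in conditional form. With a free carryover term and one change score per cycle, the treatment estimate is the cycle 1 comparison, and power at 29 per sequence is 50-52%, not 80%. Without that term, power is about 80% at zero within-participant correlation and higher at positive correlation. Four-visit models give values between these or higher. The analyses listed therefore differ widely in power on the same data, and the 80% belongs only to some of them. Separately, a non-significant carryover test on participant sums could not establish absence. These results rest on the protocol's difference and SD, a two-sided 5% test, 29 evaluable per sequence, and 38 being the SD of the analysed score. Neither the size nor the direction of any carryover bias can be fixed from the article.

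**What to change.** - **Primary model:** fit participant, period and treatment, with no carryover term and no carryover pre-test. State absence of carryover as a design assumption, supported by the stated 8-week wash-out.
- **Carryover:** replace the test of absence with a description. Compare the two sequences at week 11, adjusted for week 0, and report the estimate with its confidence interval.
- **Sensitivity analysis:** report the cycle-1-only active-sham comparison and state that its power is about 50%.
- **Sample size section:** say that 80% applies only to the analysis without a carryover term.

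The cost is a few sentences and one added analysis, all on data already scheduled. The downside is that the no-carryover assumption is put openly and a 50% figure is printed for the cycle 1 analysis. If the sponsor would rather keep a carryover-adjusted confirmatory estimate with one change score per cycle, cycle 1 needs the full 58 per group. With the same inflation that is 116/(0.95 × 0.80) = 152.6, or about 153 enrolled instead of 75.
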